## Abstract

**Background:**

Fatigue is a common and debilitating symptom for patients with incurable cancer receiving systemic treatment with palliative intent. There is evidence that non-pharmacological interventions such as graded exercise therapy (GET) or cognitive behaviour therapy (CBT) reduce cancer-related fatigue in disease-free cancer patients and in patients receiving treatment with curative intent. These interventions may also result in a reduction of fatigue in patients receiving treatment with palliative intent, by improving physical fitness (GET) or changing fatigue-related cognitions and behaviour (CBT). The primary aim of our study is to assess the efficacy of GET or CBT compared to usual care (UC) in reducing fatigue in patients with incurable cancer.

**Methods:**

The TIRED study is a multicentre three-armed randomised controlled trial (RCT) for incurable cancer patients receiving systemic treatment with palliative intent. Participants will be randomised to GET, CBT, or UC. In addition to UC, the GET group will participate in a 12-week supervised exercise programme. The CBT group will receive a 12-week CBT intervention in addition to UC. Primary and secondary outcome measures will be assessed at baseline, post-intervention (14 weeks), and at follow-up assessments (18 and 26 weeks post-randomisation). The primary outcome measure is fatigue severity (Checklist Individual Strength *subscale fatigue severity*). Secondary outcome measures are fatigue (EORTC-QLQ-C30 *subscale fatigue*), functional impairments (Sickness Impact Profile *total score*, EORTC-QLQ-C30 *subscale emotional functioning, subscale physical functioning*) and quality of life (EORTC-QLQ-C30 *subscale QoL*). Outcomes at 14 weeks (primary endpoint) of either treatment arm will be compared to those of UC participants. In addition, outcomes at 18 and 26 weeks (follow-up assessments) of either treatment arm will be compared to those of UC participants.

**Discussion:**

To our knowledge, the TIRED study is the first RCT investigating the efficacy of GET and CBT on reducing fatigue during treatment with palliative intent in incurable cancer patients. The results of this study will provide information about the possibility and efficacy of GET and CBT for severely fatigued incurable cancer patients.

**Trial registration:**

NTR3812; date of registration: 23/01/2013.

## Background

Cancer is a leading cause of mortality worldwide, with 8.2 million deaths in 2013 [1]. As a result of improvements in treatment options for certain cancers, substantial progress has been made in curative treatment of cancer. Despite these positive developments, a substantial subgroup of cancer patients will (eventually) be diagnosed with incurable cancer. The medical treatment of incurable cancer has a palliative intention, with prolonging life as one of its main aims [2]. For some cancer types, advances in cancer treatment with palliative intent have resulted in an extended period of life, resulting in more long-term or chronic cancer treatment. Next to prolonging life, treatment of incurable cancer should also be aimed at maintaining quality of life for as long as possible and relieving physical and psychological symptoms [2]. As a result of the longer-term treatment of incurable cancer patients, aspects regarding quality of life and symptom management become even more important.

### Fatigue in patients with incurable cancer

Fatigue is one of the most commonly reported symptoms during systemic treatment for incurable cancer, being reported by up to 99% of patients [3–7]. There are various ways to define fatigue, but cancer-related fatigue (CRF) is a term that is most widely used to address this symptom. The National Comprehensive Cancer Network (NCCN) defines CRF as *“a distressing, persistent, subjective sense of physical, emotional and/or cognitive tiredness or exhaustion related to cancer or cancer treatment that is not proportional to recent activity and interferes with usual functioning” *[8]. Studies show that CRF is among the most distressing symptoms [3, 9, 10] and is associated with reduced quality of life, poor performance status, and difficulty performing daily activities [3, 4, 11]. Many factors are likely to contribute to CRF in patients with incurable cancer. The multiple causes of CRF can result from the underlying disease, from secondary factors such as anaemia, infection, dehydration, and treatment side effects, or from loss of muscle mass. Apart from these physical factors, depression and anxiety can also contribute to CRF. There is also evidence suggesting that cognitive and behavioural factors, such as sleeping problems, fatigue catastrophising, and inappropriate coping are related to fatigue in patients with incurable cancer [12].

Management of CRF in incurable cancer patients should first focus on identifying and treating somatic causes, for example anaemia or hypothyroidism [8]. Yet, often no somatic cause for CRF can be found. When no somatic cause can be identified, the management of CRF can involve pharmacological treatment or non-pharmacological interventions. Thus far, no recommendation for a specific drug treatment for fatigue in palliative care patients could be given [13]. There is also no evidence-based non-pharmacological intervention for CRF in incurable cancer patients. Two non-pharmacological approaches, Graded Exercise Therapy (GET) and Cognitive Behaviour Therapy (CBT), seem promising interventions based on findings from studies addressing CRF in other cancer patients that will be discussed below.

### Exercise interventions for CRF in cancer patients

In contrast to the old advice to ‘get plenty of rest’ during cancer treatment, patients are now encouraged to optimise levels of physical activity [8]. A low level of physical activity during cancer treatment can lead to decreased physical functioning by a substantial loss of cardiopulmonary fitness and muscle mass [14]. On the other hand, increasing physical activity has been suggested as helpful in reducing CRF by improving physical capacity, resulting in a reduced effort to perform everyday activities [8]. Cramp & Byron-Daniel (2012) suggested that exercise interventions can help to reduce CRF both during and after adjuvant treatment for cancer [15]. Efficacy of exercise interventions for the subgroup of patients receiving cancer treatment with palliative intent was not examined in this Cochrane systematic review. Nonetheless, a systematic review by Lowe et al. (2009) did provide evidence that exercise interventions are feasible in patients with incurable cancer as the majority of participants were able to tolerate various physical activity interventions [16]. Three of the six reviewed studies had fatigue as one of the outcome measures and all three reported a reduction in fatigue [17–19]. However, the methodological quality of these pilot studies was evaluated as poor and only one study had a control condition [16].

Following the NCCN recommendations for exercise programs, our research group developed a 6-week GET intervention that was tailored to the physical fitness level of each participant and began at a low level of intensity and duration, progressed slowly, and was modified when the participant’s condition changed. This intervention was tested for feasibility and efficacy was explored in an uncontrolled pilot study of 26 incurable cancer patients. GET was not only feasible in terms of participants’ adherence and evaluation, but also efficacious with significant improvements in self-reported fatigue and quality of life [20]. A large-scale randomised controlled trial (RCT) is needed to confirm these promising results.

### Cognitive behaviour therapy for CRF in cancer patients

Most research on the efficacy of CBT for CRF has been done in cancer survivors or cancer patients receiving cancer treatment with curative intent. Systematic reviews and meta-analyses have indicated that CBT can reduce fatigue in cancer survivors [21, 22]. Two RCTs performed by our research group have demonstrated that fatigue and functional impairments in severely fatigued cancer survivors can be significantly reduced by CBT for CRF [23, 24]. This fatigue-specific intervention targets several cognitive-behavioural perpetuating factors of CRF. The intervention is based on the underlying assumption that cancer treatment and/or the cancer itself may trigger fatigue (precipitating factors), but that other factors such as sleep disturbance, physical inactivity, and dysfunctional thoughts about fatigue might be responsible for the persistence of fatigue (perpetuating factors) [25]. Positive intervention effects of CBT for CRF were sustained at 2-years follow-up [26]. The efficacy of CBT for CRF compared to usual care was also assessed in an RCT aimed at cancer patients during cancer treatment with curative intent [27]. Despite a significant reduction in fatigue immediately after the intervention for patients in the CBT arm, no differences were observed between these two conditions at follow-up with effects diminishing after seven months [28]. It should be noted though, that being severely fatigued was not an entry criterion for this RCT, and thus a floor effect may be present in this trial.

While there are no RCTs to date that investigated the efficacy of CBT specifically aimed at reducing fatigue in incurable cancer patients receiving cancer treatment with palliative intent, two previous RCTs provide indirect support for the positive effects of CBT on fatigue outcomes in a sample of cancer patients of whom a subgroup had incurable cancer [29, 30]. Although these RCTs did show an overall effect on fatigue, it is not clear whether this can be generalised to the group of cancer patients receiving treatment with palliative intent since subgroup analyses were not performed. Based on our previous experience with CBT for CRF in both cancer survivors and patients receiving cancer treatment with curative intent, and results of a recent study which suggested that the same perpetuating psychosocial factors are associated with fatigue in patients receiving cancer treatment with palliative intent [12], we think it is important to examine the efficacy of CBT for CRF in an RCT for this new target population.

### The role of physical activity and fitness versus fatigue-related cognitions as mediators of the reduction in CRF

Exercise interventions aiming to reduce CRF in cancer patients are based on the assumption that a lack of physical activity and deconditioning during cancer treatment can worsen fatigue [31]. It is assumed that with exercise interventions physical activity and fitness can be increased, resulting in a reduction in CRF. CBT aimed at reducing CRF in cancer patients is based on the assumption that several fatigue-related cognitions (i.e., low self-efficacy and catastrophising thoughts) and behaviours are related to the persistence of fatigue [25]. Targeting cognitions with CBT is assumed to result in less dysfunctional thoughts about fatigue, which contributes to the reduction in CRF. Although these assumptions are widespread, the role of an increase in physical activity and fitness versus a change in fatigue-related cognitions in reducing CRF has not yet been investigated in interventions for patients with incurable cancer. To investigate which factors contribute to a reduction in CRF, mediation analysis can be helpful. This technique provides insight into which factors mediate the expected reduction in CRF brought on by GET on CRF. Mediation analysis can thereby help us to better understand how interventions work [32].

### Aims of the TIRED study

We designed a multicentre RCT to test the efficacy of either GET or CBT compared to Usual Care (UC) in reducing fatigue (primary outcome) in incurable cancer patients receiving systemic treatment with palliative intent. In addition, the efficacy on improving quality of life and functional impairment will be studied. All outcomes will be assessed at baseline, and at 14, 18 and 26-weeks post-randomisation. We will assess the efficacy of GET or CBT compared to UC directly post-intervention at 14-weeks post-randomisation, which is the primary endpoint of this study. In addition, we will determine whether the expected intervention effects are sustained at follow-up assessments (18-weeks and 26-weeks post-randomisation). Furthermore, if GET and/or CBT are efficacious in reducing CRF, we will perform a mediation analysis to test if the changes in four variables (i.e., physical activity, physical fitness, self-efficacy with respect to fatigue, and/or fatigue catastrophising) mediate the reduction in fatigue.

## Methods

### Design

A non-blinded multicentre RCT (the TIRED study) will be conducted to evaluate the efficacy of GET and CBT compared to UC for severely fatigued incurable cancer patients receiving cancer treatment with palliative intent.

### Participants

Inclusion and exclusion criteria are listed in Table 1. Patients diagnosed with incurable cancer, receiving systemic treatment with palliative intent, and with a cancer treatment plan based on an expected survival of at least 6 months as judged by their oncologist, will be further assessed for eligibility by nurses and oncologists. We will include patients diagnosed with one of the following cancer types: breast, colorectal, prostate, renal cell, bladder, endometrial, ovarian, cervical, bone and soft tissue, or melanoma. Systemic cancer treatment may include chemotherapy, hormone therapy, targeted therapy, and/or immunotherapy, possibly combined with surgery and/or radiotherapy. The presence of severe fatigue reflected by a score of 35 or higher on the subscale fatigue severity of the Checklist Individual Strength (CIS-fatigue) will be used as a criterion for study entry [33].

**Table 1 Tab1:** Inclusion and exclusion criteria

Inclusion criteria	
(1)	Age ≥ 18 years.
(2)	Able to read, speak and write the Dutch language.
(3)	Diagnosis of incurable cancer (i.e. breast, colorectal, prostate, renal cell, bladder, endometrial, ovarian, cervical, bone and soft tissue cancer, or melanoma).
(4)	Scheduled for or receiving systemic cancer treatment with palliative intent (i.e., chemotherapy, and/or hormone therapy, and/or targeted therapy, and/or immunotherapy, possibly combined with surgery and/or radiotherapy).
(5)	Cancer treatment plan based on an expected survival of ≥ 6 months as judged by their oncologist.
(6)	Severely fatigued (CIS-fatigue score ≥ 35).
Exclusion criteria	
(1)	Treatable somatic cause that could explain the presence of severe fatigue (other than the underlying disease and the cancer treatment itself).
(2)	Karnofsky Performance Status < 70.
(3)	Symptomatic brain metastases.
(4)	Severe cognitive problems.
(5)	Not able to walk at least 6 min successively.
(6)	Contra-indication for physical exercise.
(7)	Current treatment by a psychiatrist or psychologist for a psychiatric disorder.

### Recruitment

Nurses and oncologists working at oncology outpatient clinics of two University-affiliated hospitals and seven Regional hospitals in the Netherlands will recruit patients. Patients will be screened for the presence of severe fatigue as part of clinical care by administering the CIS-fatigue prior to the start or during systemic treatment with palliative intent when patients visit the outpatient clinic. When eligible patients are severely fatigued, the nurse or oncologist will present the TIRED study by giving patients written information and solicit permission to have a researcher contact them. Those patients who agree to be contacted will be called by the coordinating researcher (HP), who will further inform them about the details and purpose of the study and invite them to participate. A follow-up phone call will be scheduled one week after the first phone call to address questions and determine if patients are willing to participate.

### Procedure

Eligible patients willing to participate in the study will be asked to sign informed consent upon which they will be invited by a research assistant to complete the baseline assessment (T0) at their own hospital. Upon completion of T0, the research assistant will use a central web-based randomisation service to randomly allocate a participant to one of the three study arms: (1) GET in addition to UC; (2) CBT in addition to UC; or (3) control group receiving UC (see Fig. 1). Participants assigned to GET or CBT will start the intervention approximately two weeks after T0. Both interventions will be delivered at or near their own hospital over a period of 12 weeks. Participants assigned to CBT will complete a set of additional questionnaires to determine relevant intervention modules prior to the first intervention session. Participants assigned to GET will complete an additional submaximal test to determine physical fitness during the first intervention session. At 14 weeks, participants are invited by the research assistant to complete the post-intervention assessment (T1) at the hospital. Follow-up assessments at 18 weeks (T2) and 26 weeks (T3) are entirely web-based and will be completed at home. For participants that do not have Internet access, a paper version of the follow-up questionnaires will be send to their home address, which can be returned in a self-addressed, pre-stamped envelope.

**Fig. 1 Fig1:**
[figure not shown]
Flowchart of the TIRED study

### Randomisation

A central web-based randomisation service provided by an independent statistician will be used. Randomisation will be stratified by centre. We will use block randomisation to reach the same number of participants in all study arms. The ordering of blocks and their respective size will be unknown for the research assistants and coordinating researcher. When possible, minimisation on gender will be performed in order to balance the gender distribution in all study arms. If block randomisation restricts the choice to two or only one study arm, minimisation will always be overruled by block randomisation. A research assistant will perform allocation upon completion of T0 in the presence of the participant.

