### Statistical analyses

The statistician who will perform data analyses will be blinded for intervention allocation. To test the efficacy of both interventions compared to UC, an ANCOVA will be performed for each intervention with *fatigue severity* (CIS-fatigue) at T1 as dependent measure, condition as fixed factor and CIS-fatigue screening score as covariate [47]. Missing data is a common problem in palliative care research and is also anticipated in our study as a result of deteriorating health or because the patient has died. Data will be primarily analysed on complete case basis, i.e. only data from evaluable participants with a T1 assessment will be used. The *p*-level is adjusted to 0.025 to account for the two primary analyses, i.e., GET versus UC and CBT versus UC. When statistically significant differences between GET versus UC and/or CBT versus UC are found, additional sensitivity analysis accounting for all randomised participants will be done to explore the impact of missing data. Several methods of imputation are available and the choice will depend on the actual circumstances of missing data. We will record the causes of missing data and careful considerations will be given to which imputation procedure should be used.

In addition, ANCOVA will be performed for the secondary outcomes (*fatigue, quality of life, and functional impairments*), with baseline score (T0) on the dependent measure as covariate. In these exploratory analyses a *p*-level of 0.05 will be used. Longer-term follow-up effects at T2 and T3 will also be tested using ANCOVA, with baseline score (T0) on the dependent measure as covariate. Again, in these explorative analyses a *p*-level of 0.05 will be used. No sensitivity analysis will be done, as the power for follow-up analyses will be limited due to the expected significant amount of attrition.

Mediation analysis will be conducted to explore the possible underlying mechanisms of the expected reduction in fatigue severity (CIS-fatigue) brought on by GET and CBT at T1. Following recommendations of Preacher and Hayes (2008) [48], we will perform multiple mediation analysis using bootstrapping to test the mediating effect of four potential mediators (i.e., changes in *physical activity, physical fitness, self-efficacy with respect to fatigue, and catastrophising in response to fatigue*). We will only perform multiple mediation analysis when there is a significant effect of one or both interventions compared to UC.

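### The stated ANCOVAs leave out the factors that randomisation balances (centre, and partly gender); if these predict fatigue, standard errors are conservative and some achievable precision is forgone

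*Protocol article*

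**What the plan says.** The Randomisation section of the protocol article names two balancing factors. The first is centre: "Randomisation will be stratified by centre". The Recruitment section puts the number of centres at nine: "two University-affiliated hospitals and seven Regional hospitals in the Netherlands will recruit patients". Blocks serve to equalise arm sizes: "We will use block randomisation to reach the same number of participants in all study arms". The second factor is gender, in a weaker form: "When possible, minimisation on gender will be performed in order to balance the gender distribution in all study arms". Where a block leaves only one or two arms open, "minimisation will always be overruled by block randomisation".

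The Statistical analyses section then writes out the models. The primary ANCOVA, fitted separately for each intervention against usual care, has "condition as fixed factor and CIS-fatigue screening score as covariate". The secondary-outcome and T2/T3 models are ANCOVAs "with baseline score (T0) on the dependent measure as covariate". Centre and gender appear in none of them, and no reason is given for leaving them out.

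**The concern.** Balancing the arms on a factor that predicts the outcome removes that factor's contribution from the chance difference between arms. A model without the factor still counts its variation as residual noise. The reported standard error then exceeds the true sampling variability, confidence intervals are wider than they need be, and the test runs somewhat below its nominal level.

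The article makes some prognostic difference plausible without measuring it. The nine hospitals are of two types, the collaboration grew during the trial, eligibility was widened beyond breast and colorectal cancer, and several of the eligible tumours are sex-linked. The plan also expects little from its single covariate: the sample-size section assumes a correlation of 0.10, which is 0.10² = 1% of outcome variance. A centre share of even 5% would exceed that. Recruitment is reported as difficult, so recoverable precision has some value.

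**Working it through.** **Inputs from the article.** Difference 6 points; two-sided alpha 0.025 per comparison; power 0.80; 51 evaluable per arm; 30% attrition; 219 in total; nine centres; T0–T1 correlation 0.10; complete cases at T1.

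**Inputs not in the article, hence assumed.** The SD of CIS-fatigue, and the shares of outcome variance due to centre and gender.

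**Step 1: the plan's own figure.** 51 / (1 − 0.30) = 72.9, rounded up to 73 per arm; 73 × 3 = 219. This matches.

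**Step 2: the implied SD.** Solving n = 2·SD²·(z₀.₉₈₇₅ + z₀.₈₀)² / 6² for n = 51 gives SD ≈ 9.8. The noncentral t calculation gives SD ≈ 9.7, which is used below. The 51 is therefore consistent with the inputs, but it cannot be confirmed independently because no SD is stated.

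**Step 3: what theory predicts.** If a fully balanced factor explains a share R² of the variance and is left out, the model standard error is too large by about 1/√(1 − R²): 1.04 at 7%, 1.08 at 15% and 1.15 at 25%. These are upper limits here, because gender is only partly balanced and attrition disturbs the balance by centre.

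**Step 4: simulation of the design.** There were 4,000 replicates per scenario under the null and 4,000 under a 6-point effect. Each trial had 219 patients in nine unequal centres, with three-arm blocks of 3 or 6 within centre. Gender (35% in one group) was minimised only while all three arms were open. Attrition was 30% at random. Each pairwise ANCOVA was fitted to the same data with and without gender and fixed centre effects.

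| Centre / gender share | Model SE ÷ true SE, stated model | Type I error, stated model (nominal 0.025) | Power, stated model | Power, centre + gender added | Change (points) |
|---|---|---|---|---|---|
| 0% / 0% | 1.00 | 0.027 | 0.795 | 0.776 | −1.9 |
| 2% / 1% | 1.00 | 0.024 | 0.801 | 0.797 | −0.4 |
| 5% / 2% | 1.03 | 0.023 | 0.803 | 0.813 | +1.0 |
| 10% / 5% | 1.05 | 0.020 | 0.814 | 0.853 | +3.9 |
| 20% / 5% | 1.09 | 0.016 | 0.826 | 0.888 | +6.2 |

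The Monte Carlo error of a type I figure is √(0.025 × 0.975 / 4000) ≈ 0.0025. The 0.027, 0.024 and 0.023 therefore cannot be told apart from 0.025; the shortfall is clear only in the last row and suggestive at 10%/5%. In the adjusted model the ratio of model to true standard error stayed between 0.99 and 1.01 throughout.

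**Step 5: degrees of freedom.** Fixed effects for nine centres use 8 and gender uses 1, so 9 in all. With 2 × 51 = 102 patients in a comparison, residual degrees of freedom fall from 102 − 3 = 99 to 102 − 12 = 90. This is the source of the small loss in the first two rows.

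**The case against.** The strongest reply is that nothing the plan promised is lost. The 51 per arm was sized for a t-test with no reduction for covariates, and the stated model delivers 0.795 to 0.826 power in every scenario. Any error is on the conservative side. All of this stands.

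The benefit also depends on a quantity the article does not give. If centre and gender together explain 3% or less of the variance, adjustment gains nothing and costs 0.4 to 2 points. Cancer treatment follows national and regional guidelines at every centre, which may keep centre differences small. Local delivery of the interventions points more to effects that vary by centre than to a shared centre effect on fatigue. This too stands, and it is why the point is conditional.

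Gender is the weaker of the two factors. Because blocks overrule minimisation, its balance is only partial, so it contributes less than centre to any overstatement of the standard error.

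A separate analysis plan might add these terms. The article nevertheless lists the model terms itself, so such a plan would depart from the published text and the two would need reconciling.

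**Conclusion.** The mismatch between randomisation and analysis is in the text, and its direction is clear: if centre or gender predicts CIS-fatigue, the standard errors are conservative. The size is uncertain. Assuming an SD of about 9.7 and random attrition, adjustment changes power by between about −2 points (no prognostic value) and about +6 points (25% of variance explained). At a combined share of about 7%, the gain is about 1 point and the standard error is about 3% too large.

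A reader might go further and infer that power falls short of plan, that the standard errors are certainly too large, that the benefit of balancing is thrown away, or that adjustment is free. None of these is supported. Planned power of about 0.80 holds throughout, and the overstatement requires prognostic factors that the article does not quantify. Balance lowers the true sampling variance whichever model is fitted, so power under the stated model rises with the prognostic share and only part of the benefit is forgone. Adjustment also uses degrees of freedom. There is no excess false-positive risk. This is a modest efficiency point and not a threat to validity.

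**What to change.** Before analysis, add centre and gender to the primary ANCOVA for each comparison, and use the same terms in the secondary and follow-up models so that all results rest on one specification. Enter centre as a random intercept, or as a fixed effect with a rule for pooling small centres that is set in advance and does not depend on outcome data. State which is chosen. If the factors are to stay out, say so and give the reason; either way, a later choice between adjusted and unadjusted results is closed off.

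The cost is a short amendment to the analysis text and about 9 degrees of freedom per comparison with fixed centre effects, or fewer with pooling or a random intercept. If neither factor proves prognostic, the price with fixed effects is up to about 2 points of power.
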